**1. Study Purpose**

To explore the change in serum metabolites of the pancreatic cancer patients with cachexia and without cachexia

**2. Background**

**2.1. Pancreatic cancer and cachexia**

Pancreatic cancer is the leading cause of cancer-related death. At the time of diagnosis, tumor resection with curative intent is only possible in 10%to 15% of subjects, leaving a large population with poor prognosis and limited therapeutic options. Overall, the 5-year survival rate is only about 4%.

Some patients with advanced or end-stage pancreatic cancer experience debilitating symptoms such as weight loss, emaciation, hypoproteinemia, and edema, also known as cachexia. These symptoms may be caused by changes in carbohydrate/protein metabolism experienced as the disease progresses. While secretion of inflammatory cytokines (IL1, IL6, TNF-α, TGF-β, etc.) and vascular endothelial growth factors (VEGFs) has been reported to be involved in the pathophysiology of cachexia, the precise mechanism of cachexia are unknown [1, 2].

Clarification of the mechanism of cachexia may require comparison of pathophysiological changes between cancer patients with and without cachexia. In addition, the physiology of living organisms is known to be affected by circadian rhythms. We think that effects of circadian rhythms may need to be considered in the evaluation of metabolic changes associated with cachexia [3, 4].

**2.2. Metabolomics**

While genes are commonly considered the “blueprint of life,” in actuality, many proteins and metabolites play essential roles in organic activities. An exhaustive analysis of metabolites produced by living organisms is called metabolomics. This analysis, which involves a pattern analysis of a series of changes in metabolites associated with the development of a certain disease, assesses multiple biomarkers rather than a single one for the disease and is therefore expected to help elucidate unknown disease pathologies.

Briefly, water-soluble and lipid-soluble metabolites are separately extracted from biological specimens such as serum (or plasma), urine, exhaled breath condensate, tissues, and feces, and metabolites with a mass number of 1,000 or less are measured using liquid chromatography/mass spectrometry and gas chromatography/mass spectrometry. After data mining, a principal component analysis as metabolic fingerprinting is performed to determine the pattern of metabolite production specific to the disease itself, stage of progression, and malignancy grade, parameters which can be used to diagnose pathological conditions. This information is also expected to be useful in identifying individual metabolites as metabolite profiling and establishing an early diagnosis system using these metabolites as biomarkers.

Most currently used disease-specific biomarkers are proteins. However, since these vital functions are often directly controlled by low-molecular metabolites affected by those proteins, these metabolites in conducting early diagnosis and in tracing the pathology of various diseases may be useful as biomarker.

**3. Methods**

**3.1. Subjects**

**T**he pancreatic cancer patients with cachexia (n=10) and without cachexia (n=10)

- Control : PS 0-2, Alb ≧ 3.5mg/dL, Anorexia Gr 0-1, Weight loss < 5% over past 6 months
- Cachexia : PS 1-4, Anorexia Gr1-4, Weight loss > 10% over past 6 months

**3.2. Significance of the study**

We investigated the difference in serum metabolites of pancreatic cancer patients with and without cachexia and analyzed the pattern and intra-day variation in metabolites using metabolomics. Our findings here may help improve treatment of patients with cachexia if specific metabolites or metabolic changes involved in cachexia can be identified.

**3.3 Criteria for subject enrollment**

**3.3.1. Eligibility criteria**

1) Patients histologically confirmed adenocarcinoma or adenosquamous carcinoma of the pancreas.

2) Locally advancer or metastatic pancreatic cancer (UICCC TNM classification Stage IVA-IVB).

3) (a) Control: PS 0-2, Alb ≧ 3.5mg/dL, Anorexia Gr 0-1 (NCI-CTC ver.3), Weight loss < 5% over past 6 months

(b) Cachexia: PS 1-4, Anorexia Gr1-4, Weight loss > 10% over past 6 months

4) Patients 20 years of age or older.

5) Patients with adequate organ function as follows:

Liver function: AST and ALT less than 2.5 times of ULN.

Total bilirubin value less than 1.5 times of ULN.

Renal function: Serum creatinine level less than 1.5 times of ULN.

6) Patients from whom written informed consent for participation in the study is obtained.

**3.3.2. Exclusion criteria**

1) Surgically resectable pancreatic cancer.

2) Patients with pancreatic neuroendocrine tumor.

3) Patients treated with chemotherapy within 7 days.

4) Patients undergone surgery within 28 days.

5) Patients treated with definitive irradiation within 28 days or palliative irradiation within 14 days.

6) Patients with active multiple primary cancer.

7) Patients with serious pre-existing medical condition such as uncontrolled infection, diabetic mellitus (ex. HbA1c level greater than 8.0%).

8) Patients taking concomitant steroids.

9) In addition, patients who the investigator determines to be unsuitable for the study.

**3.4. Collection of samples**

**3.4.1. Serum samples for metabolomics and serum markers**

Blood samples will be collected (approximately 5 ml of whole blood) at 6:30 AM, 11:30 AM, 4:30 PM, and 9:30 PM to analyze the intra-day variation. After collection of whole blood, samples were allowed to clot at room temperature, and serum was separated by centrifugation at 3,000×g for 10 min at 4 °C and stored at -80 °C until use.

**3.4.2.** **Anonymity of samples**

Samples will be managed and anonymized at the time of registration by the personal data manager. The personal data and case-coding correspondence table will be stored to ensure that only the personal data manager can access them.

**3.5. Measurement of serum markers**

Serum IL-6, TNFα, and leptin were measured by SRL Inc. (Tokyo, Japan).

**3.6. Metabolomics**

**3.6.1. Equipment**

- Liquid chromatography/mass spectrometer; LCMS-IT-TOF (Shimadzu Corporation)
- Gas chromatography/mass spectrometer; GCMS-2010 (Shimadzu Corporation)

**3.6.2. Metabolome analysis using a liquid chromatography/mass spectrometer**

**Preparing of samples; Measurement of water-soluble metabolites in serum**

Ten microliters of serum and 10 μL of internal standard (e.g. 50 μg/mL 2-isopropylmalic acid) were placed into a 1.5-mL Eppendorf tube. Methanol (0.5 mL) was then added and mixed, followed by 0.25 mL of distilled water and then 0.5 mL of chloroform. Subsequently, the mixture was incubated with rotation (1200 rpm) for 30 minutes at 37 °C. The solution was centrifuged at 15000 rpm for 5 minutes at 4 °C, and 200 μL of the supernatant was collected in another 1.5-mL Eppendorf tube and concentrated using a SpeedVac centrifugal concentrator. The solution was then lyophilized to dryness using a lyophilizer. The residue was rehydrated in 75 μL of 5% acetonitrile solution and filtered using a 0.22-μm filter spin column. Fifteen microliters of the filtrate was used for measurement with a LCMS-IT-TOF.

**Data processing**

The mass chromatogram obtained by LCMS-IT-TOF was processed using the data processing software of IonXtractView for data picking to quantify the data of peak intensity and m/z. Data of each sample were normalized based on the peak intensity of 2-isopropylmalic acid (m/z: 175.01) as an internal standard.

**3.6.3. Metabolomic analysis with the use of a gas chromatography/mass spectrometer**

**Pretreatment of samples; Measurement of water-soluble metabolites in serum (or plasma)**

Ten microliters of serum (or plasma) and 50 μL of mixed solvent (methanol:chlorofor:water = 2.5:1:1) were placed into a 1.5-mL Eppendorf tube and mixed, after which 10 μL of 1 mg/mL 2-isopropylmalic acid (internal standard) was added and mixed. Subsequently, the mixture was incubated with rotation (1200 rpm) for 30 minutes at 37 °C. The solution was centrifuged at 15000 rpm for 3 minutes at 4 °C, and 45 μL of the supernatant was collected in another 1.5-mL Eppendorf tube. Then, 40 μL of ultrapure water was added and mixed, and the mixture was centrifuged at 15000 rpm for 3 minutes at 4 °C. Fifty microliters of the supernatant was collected in a third 1.5-mL Eppendorf tube and concentrated using a SpeedVac centrifugal concentrator. The solution was then lyophilized to dryness using a lyophilizer. The residue was rehydrated in 20 μL of 20 mg/mL methoxyamine pyridine solution and ultrasonicated in a water bath for 20 minutes. Subsequently, the solution was incubated with rotation (1200 rpm) for 90 minutes at 30 °C, and 10 μL of MSTFA was added. The mixture was then incubated for a further 30 minutes at 37 °C and then centrifuged at 15000 rpm for 3 minutes at 4°C. The supernatant was used for measurement with a GCMS-2010.

**Measurement with a GCMS-2010**

GC/MS analysis was performed using a GCMS-QP2010 Ultra (Shimadzu Co., Kyoto, Japan) with a fused silica capillary column (CP-SIL 8 CB low bleed/MS; inner diameter, 30 mm × 0.25 mm; film thickness, 0.25 μm; Agilent Co., Palo Alto, CA), according to a previously described method {Tsugawa, 2011 #43}. The front inlet temperature was 230oC, and the flow rate of helium gas through the column was 39.0 cm/sec. The column temperature was held at 80oC for 2 min and then raised by 15oC/min to 330oC and held there for 6 min. The transfer line and ion-source temperatures were 250oC and 200oC, respectively. Twenty scans per second were recorded over the mass range 85-500 m/z using the Advanced Scanning Speed Protocol (ASSP, Shimadzu Co.).

**Data processing**

Data processing was performed according to the methods described in previous reports {Tsugawa, 2011 #43}{Tsugawa, 2011 #28}. Briefly, the MS data were exported in netCDF format. The peak detection and alignment were performed using the MetAlign software (Wageningen UR, The Netherlands). The resultant data were exported in CSV format and then analyzed with in-house analytical software. For semi-quantification, the peak height of each ion was calculated and normalized to the peak height of 2-isopropylmalic acid as an internal standard. Names were assigned to each metabolite peak based on the method described in a previous report{Tsugawa, 2011 #28}.

**4. Evaluation items**

1) Patient characteristics: gender, age at time of registration, date of birth, and patient identification number.

2) General findings: Performance status, height, weight and vital signs.

3) Tumor findings: pathological diagnosis, and clinical stage (TNM classification).

4) Hematology findings: CBC, TP, Alb, T-Bil, AST, ALT, LDH, Amy, BUN, Cr, T-Chol, LDL, HDL, TG, CRP, Glu, HbA1c and Tumor markers including CEA, CA19-9, and DUPAN-2.

5) Concomitant medications.

**5. Endpoint and Statistical considerations**

**5.1. Endpoint**

Primary endpoint：identification of cachexia-related metabolites by metabolomics.

Secondary endpoints：intra-day variation in the metabolites involved in cachexia; changes in the level of serological markers involved in cachexia, such as inflammatory cytokines (e.g. IL-6, TNFα) and leptin, in the presence or absence of cachexia; and changes in QOL survey results in the presence or absence of cachexia.

**5.2. Rationale for sample size**

The present study featured 10 subjects per group, as although this study was exploratory in nature and therefore involved no statistical rationale for sample size calculation, preceding studies on metabolomics have indicated significant results with a sample size of approximately 10 subjects per group. However, if a more useful analysis method found is found that may be implemented in the study, the analysis methods may be altered and the necessary sample size recalculated.

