**5.3. Statistical analysis**

Data are expressed as the mean ± standard error. Levels of serological markers and metabolites between the cohorts with and without cachexia were compared using the Mann-Whitney U test or Wilcoxon Signed-Rank test. Kruskal-Wallis multiple comparison (z-test) with bonferroni correction was then used to compare values for each metabolite across all 4 time points tested to determine if there are intra-day variances in the metabolite. Survival time was estimated using the Kaplan-Meier method.

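### Section 5.2 lets the analysis method and sample size change without requiring that this precede, or be blind to, the cohort comparison, so false positives could rise

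*Protocol*

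**What the plan says.** Section 5.2 of the Protocol sets the size plainly: "The present study featured 10 subjects per group". It adds that the study is exploratory and "involved no statistical rationale for sample size calculation". It then opens both the method and the size to change: "if a more useful analysis method found is found that may be implemented in the study", then "the analysis methods may be altered and the necessary sample size recalculated". No timing, blinding condition, criterion for usefulness or error adjustment goes with this permission, and nothing requires the planned analysis to be reported alongside the new one.

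The primary endpoint in section 5.1 is "identification of cachexia-related metabolites by metabolomics". The analysis that serves it is in section 5.3, where levels in the two cohorts "were compared using the Mann-Whitney U test or Wilcoxon Signed-Rank test". No rule says which of the two tests applies.

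**The concern.** Whether a metabolite counts as identified depends on a between-cohort test. A method can seem more useful simply because it flags more metabolites, and more patients can seem necessary simply because the first comparison was not significant. Nothing in section 5.2 excludes either reason. If the permission were used in that way, the nominal error rate of each test would no longer be the actual one, and a reader of the results could not tell a planned finding from one produced by the change.

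Section 5.3 adds to the difficulty. Two tests are joined by an or, and one of them, the signed-rank test, is for paired data and does not suit two independent groups of patients. Even before section 5.2 is invoked, the cohort comparison is not tied to one test.

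**Working it through.** **The plan's own figure.** The 10 per group cannot be reproduced, because the Protocol gives no significance level, power, effect size or standard deviation. It says as much, so there is no stated calculation to check.

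**Inputs from the Protocol.** 10 patients per group (sections 3.1 and 5.2); Mann-Whitney or signed-rank for the cohort comparison (section 5.3).

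**Assumptions not in the Protocol.** Two-sided 5% per metabolite; extension to 15 or 20 per group; the t-test as a further candidate method; arbitrary pairing of patients so that the signed-rank test can be run at all.

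**Method.** One metabolite with no true cohort difference was simulated 20,000 times, once with normal and once with lognormal data, using exact rank tests. For each strategy, the false-positive rate is the share of replicates in which at least one of the permitted tests gives p < 0.05. The Monte Carlo standard error near 8% is √(0.08 × 0.92 / 20,000) ≈ 0.002, or 0.2 percentage points.

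| Strategy | Normal | Lognormal |
|---|---|---|
| Mann-Whitney at 10 v 10, fixed in advance | 4.6% | 4.1% |
| Signed-rank at 10 v 10 alone | 5.1% | 5.0% |
| Better of Mann-Whitney and signed-rank | 6.6% | 6.5% |
| Best of those two and the t-test | 7.4% | 6.8% |
| Mann-Whitney at 10 v 10, then at 20 v 20 if not significant | 8.1% | 7.8% |
| Mann-Whitney at 10, 15 and 20 per group | 9.6% | 9.1% |
| Either named test at 10 v 10, then Mann-Whitney at 20 v 20 | 9.8% | 9.9% |

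A milder rule, extending to 20 v 20 only if the first p-value is below 0.20, gave 6.1% and 6.5% in two separate simulations. The range is therefore about 6% to 10%. Relative to the assumed level, that is 6.1 / 5 ≈ 1.2 times to 9.9 / 5 ≈ 2 times.

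**When nothing is inflated.** If the method or size is changed without sight of cohort-labelled results, the choice does not depend on the group difference. A single valid test at the final size then rejects at most 5% of the time under no difference. The first row of the table is the example: one exact Mann-Whitney test at a fixed size stays below 5%.

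**Comparison with multiplicity.** Section 5.3 mentions Bonferroni only for the time points: "Kruskal-Wallis multiple comparison (z-test) with bonferroni correction was then used to compare values for each metabolite across all 4 time points". With m independent metabolites each tested at an assumed 5% and no correction between cohorts, the chance of at least one false positive is 1 − 0.95^m: 64% for m = 20, 92% for m = 50 and 99.4% for m = 100. The Protocol does not state m. This arises even if section 5.2 is never used. For an assumed m = 100, using the permission to extend would move the expected number of false identifications from about 4.1–4.6 (100 × 0.041 to 100 × 0.046) to about 7.8–8.1.

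**The case against.** The strongest reply is that section 5.2 ties a change to a better method, not to an unwelcome result, and that the study declares itself exploratory. Freezing of methods and labelling of later ones is commonly left to a statistical analysis plan, which may exist but is not shown. Analysis method might also mean the assay, since the headings of sections 3.6.2 and 3.6.3 use analysis for the mass-spectrometry work, and adopting a better assay is not test-shopping.

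Much of this stands. A reader might infer that the Protocol allows changes at any time, including after the cohort comparison has been seen. It does not say so; that reading comes from silence. A reader might also infer that the clause in itself inflates error. It does so only if used after a look, and only relative to a level that has to be assumed. The scenarios with 15 or 20 per group or a t-test go beyond what the Protocol names. Uncorrected testing of many metabolites is the larger source of false positives.

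A further tempting reading is that the rationale for size is a defect to be cured with a detectable difference, since it rests on "preceding studies on metabolomics have indicated significant results with a sample size of approximately 10 subjects per group". That does not hold as a finding: the Protocol claims no power and openly disclaims a statistical rationale, so there is no false figure to correct.

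The permission itself remains. It is an affirmative, open-ended statement under the heading on endpoint and statistical considerations, so the statistical reading is the natural one, and an analysis plan would have to restrict it. Being exploratory excuses the absence of a power calculation. It does not remove the need to separate planned from post hoc analyses.

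**Conclusion.** The point holds in a limited form. Section 5.2 permits the method and the sample size to change without requiring that this come before, or be blind to, the between-cohort comparison. If the permission is used after a look at the cohort data, the per-metabolite false-positive rate could rise from an assumed 5% to about 6% to 10%: about 6.5% using only the two tests the Protocol names, and about 8% for one unadjusted extension to an assumed 20 v 20. Used blind, with one valid test at the end, it does no harm to the error rate. The documents do not show that a change after a look is intended. In an exploratory study this is a moderate matter of fixing and labelling the analysis, worth correcting because the correction is so cheap.

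**What to change.** Replace the last sentence of section 5.2 with a rule to this effect:

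- One test for the two independent cohorts, the Mann-Whitney test, and the sample size are fixed before the first between-cohort comparison.
- Any change to either is documented, dated and made without sight of cohort-labelled results.
- Any method or patients added later are reported as post hoc, beside the planned analysis.

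In section 5.3, remove the signed-rank alternative from the cohort comparison. Freezing that section as it stands would keep the choice between two tests, and with it the 6.5% to 6.6% rate, and would lock in a paired test for unpaired groups.

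The cost is a few sentences. No patients or assays are added and better methods are not forbidden; the only loss is a little freedom to present a later method as the planned one.

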**5.3. Statistical analysis**

Data are expressed as the mean ± standard error. Levels of serological markers and metabolites between the cohorts with and without cachexia were compared using the Mann-Whitney U test or Wilcoxon Signed-Rank test. Kruskal-Wallis multiple comparison (z-test) with bonferroni correction was then used to compare values for each metabolite across all 4 time points tested to determine if there are intra-day variances in the metabolite. Survival time was estimated using the Kaplan-Meier method.

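### Section 5.3 summarises all data as mean ± standard error but compares levels only with rank tests on 10 patients per cohort; a summary that matches the test is a cheap, minor reporting improvement.

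*Protocol*

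**What the plan says.** Protocol Section 5.3 opens with a general rule: "Data are expressed as the mean ± standard error". It then says that levels of serological markers and metabolites in the two cohorts "were compared using the Mann-Whitney U test or Wilcoxon Signed-Rank test". For intra-day variation, "Kruskal-Wallis multiple comparison (z-test) with bonferroni correction was then used to compare values for each metabolite across all 4 time points". Every planned comparison of levels is therefore rank-based.

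Section 5.2 gives the size, "The present study featured 10 subjects per group", and says that the study "involved no statistical rationale for sample size calculation". For GC/MS, the data-processing text in Section 3.6.3 describes a semi-quantitative ratio: "the peak height of each ion was calculated and normalized to the peak height of 2-isopropylmalic acid as an internal standard". LC/MS intensities are likewise normalised to an internal standard (Section 3.6.2). The secondary endpoints in Section 5.1 add "changes in the level of serological markers involved in cachexia, such as inflammatory cytokines (e.g. IL-6, TNFα) and leptin".

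The protocol names no median, quartiles, SD or range.

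**The concern.** Rank tests are a sensible choice for non-negative ratios and cytokine levels in small groups, where skew is plausible. The mean with its standard error is a different kind of summary. One or two patients can drive it, it describes the precision of a mean and not the spread between patients, and it does not estimate what the Mann-Whitney test addresses.

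With no power claim behind the sample size, the size and uncertainty of each cohort difference are a large part of what the study can offer. Readers commonly take separated SE bars as a sign of a real difference. If bars separate often when the planned test finds nothing, the tables and figures give a more favourable impression than the analysis supports.

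**Working it through.** The protocol gives no alpha, power, SD or effect size, so there is no stated figure to reproduce.

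**Inputs from the protocol:** n = 10 per cohort (Sections 3.1 and 5.2); summary by mean ± SE and comparison by rank tests (Section 5.3).

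**Assumptions, not in the protocol:** two-sided alpha of 0.05; log-normal values with log-SD from 0.3 to 1.5; a shift between cohorts of 0 to 1.33 log-SDs. There were 20,000 simulated data sets per setting.

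**1. SE against spread.** SE = SD/√n = SD/√10 = 0.316 SD. Bars read as patient spread are too short by a factor of √10 = 3.16.

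**2. Coverage of mean ± SE.** For normal data this is P(|t| < 1) on 9 df = 0.657, about 66%. By simulation it is 58% for log-normal data with log-SD 1 and 50% with log-SD 1.5.

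**3. Bars that just touch.** With equal SEs the means differ by 2 SE, and the standard error of the difference is √2 SE. So t = 2/√2 = 1.41 on 18 df, which gives p = 0.17 (a t-test p-value). The 95% half-width for the difference in means is t(0.975, 18 df) × √2 × SE = 2.97 SE, or 0.94 SD.

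**4. Bars against the Mann-Whitney test.** At 10 v 10 the exact two-sided test rejects when the smaller U is 23 or less (actual size 0.0433). With a shift of 0.5 log-SD:

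| log-SD | Test significant | Bars separated, given not significant | Bars overlap, given significant | Means reversed, given significant |
|---|---|---|---|---|
| 0.3 | 16.4% | 29.4% | 0.6% | 0% |
| 0.5 | 16.5% | 30.3% | 1.8% | 0% |
| 1.0 | 16.6% | 31.4% | 6.6% | 0.4% |
| 1.5 | 16.3% | 32.6% | 10.6% | 1.3% |

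The usual conflict is separated bars with a non-significant test. Over all the shifts tried, the means were reversed in 0% to 2.2% of significant results.

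**5. Feasibility of a matching summary.** The Hodges-Lehmann difference is the median of the 10 × 10 = 100 pairwise differences. Its interval runs from the 24th smallest to the 24th largest, with exact coverage 1 − 0.0433 = 95.7%.

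An invented and deliberately extreme example shows the behaviour. Controls are 1.0, 1.1, …, 1.8 and one value of 20; cachexia patients are 2.0, 2.1, …, 2.9. Mean ± SE gives 3.26 ± 1.86 v 2.45 ± 0.10. The medians are 1.45 v 2.45, and the Hodges-Lehmann difference is +1.0 (0.6 to 1.3), in line with a Mann-Whitney p of 0.0015. Step 4 shows how rarely such a reversal should be expected.

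**The case against.** The standard error is a correct measure of the precision of a mean, and the plan labels it as such. With n stated, any reader can recover SD = 3.16 × SE. The 66% figure is simply what a one-SE bar is at this sample size, and the protocol never calls it a 95% interval. All of this stands. It limits the point to how the summary fits the test; it does not make the summary wrong.

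A reader might infer that the display would mislead the choice of cachexia-related metabolites. The protocol does not support that. Levels are compared by the rank tests, and nothing says that candidates are picked from means or bars. The significant metabolites are the same under either display.

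A reader might also infer that the means will often contradict the test in direction. Counted over all data sets, disagreement is more frequent, but nearly all of it arises where the rank test is not significant and neither direction carries much meaning. At log-SD 1.5 and a shift of 0.5 log-SD, reversed and significant together is 0.163 × 0.0129 = 0.0021, about 0.2% of data sets.

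Finally, the absence of a planned interval for the cohort difference is not a fault by itself, since a statistical analysis plan that is not shown could supply one. Section 5.2 also allows the analysis methods to change. What remains is that Section 5.3 itself states the summary rule, and that rule does not match the tests named beside it.

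**Conclusion.** The point holds as a minor reporting improvement. Without any distributional assumption, at n = 10 the SE is 0.32 SD and the mean is not what the rank test compares. With normal data, mean ± SE is about a 66% interval, and equal bars that just touch correspond to p = 0.17. The 58% and 50% coverage figures, the 30% to 33% of non-significant data sets with separated bars, and the roughly 0% to 2% of significant results with reversed means all rest on assumed log-normal data. The protocol gives no distribution or SD.

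It does not follow that any test is invalid, that an error rate changes, or that the wrong metabolites would be selected.

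**What to change.** Replace the opening sentence of Section 5.3 with a rule that markers and metabolites are summarised by median and interquartile range per cohort, with n counted in patients. Beside each Mann-Whitney p-value, report the Hodges-Lehmann difference between cohorts (or the ratio, on the log scale) with its 95% confidence interval, so that the reported size and uncertainty match the test.

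The cost is a change of wording and slightly more output from standard software. No new data are needed and the tests stay as they are. The displays will look wider and less favourable.

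### The primary endpoint is a list of cachexia-related metabolites, but the between-cohort tests that produce it have no error control across metabolites and no rule for declaring a metabolite related

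*Protocol*

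**What the plan says.** Protocol section 5.1 sets the primary endpoint as "identification of cachexia-related metabolites by metabolomics". Section 5.3 gives the between-cohort analysis: "Levels of serological markers and metabolites between the cohorts with and without cachexia were compared using the Mann-Whitney U test", with the Wilcoxon signed-rank test named as an alternative. No adjustment, false discovery rule, effect-size filter or validation step accompanies that sentence.

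The one multiplicity correction named comes next and concerns the time of day: "Kruskal-Wallis multiple comparison (z-test) with bonferroni correction was then used to compare values for each metabolite across all 4 time points tested".

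On scale, section 2.2 introduces the technique broadly ("An exhaustive analysis of metabolites produced by living organisms is called metabolomics"), and section 3.6 measures serum on two platforms, LC/MS and GC/MS. The number of metabolites to be tested is not given. Section 3.4.1 takes four samples per patient, "at 6:30 AM, 11:30 AM, 4:30 PM, and 9:30 PM to analyze the intra-day variation", and section 5.3 does not say which of them enters the between-cohort test. Section 5.2 fixes 10 subjects per group and explains that "this study was exploratory in nature and therefore involved no statistical rationale for sample size calculation".

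**The concern.** The primary result is the list itself. A reader of that list needs to know roughly how many of its entries would be there if cachexia had no effect on any metabolite. With many metabolites, two small cohorts, and neither an error rate nor a declaration rule fixed in advance, that cannot be known. The choice among four samples per patient adds a second, unstated layer of selection. Section 5.2 also allows the analysis methods to be altered, so nothing in the protocol prevents the criterion from being settled after the data are seen. At stake is which metabolites are carried forward as candidate markers or mechanisms of cachexia.

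**Working it through.** **Plan's own figure.** The only design figure is 10 per group. It cannot be reproduced, because section 5.2 gives no significance level, power, effect or SD and disclaims a calculation.

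**Inputs.** From the protocol: 10 v 10, a Mann-Whitney test per metabolite, four samples per patient. Assumed, because the protocol is silent: two-sided 0.05, with 0.01 as a strict alternative; 50, 100 or 200 metabolites.

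**Step 1: exact size of one test.** At 10 v 10 there are C(20,10) = 184,756 equally likely rank arrangements under the null.
- At 0.05 the test rejects at U ≤ 23: size 2 × P(U ≤ 23) = 0.0433. The next step, U ≤ 24, gives 0.0524 and is too large.
- At 0.01 it rejects at U ≤ 16: size 0.0089.
- The smallest attainable p is 2 / 184,756 = 0.0000108.

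**Step 2: no metabolite differs, each tested once.** Expected false identifications = m × size. Chance of at least one = 1 − (1 − size)^m, which needs independent metabolites; the expected count does not.

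| m | Expected at 0.05 | At least one at 0.05 | Expected at 0.01 |
|---|---|---|---|
| 50 | 50 × 0.0433 = 2.2 | 89% | 0.4 |
| 100 | 100 × 0.0433 = 4.3 | 98.8% | 0.9 |
| 200 | 200 × 0.0433 = 8.7 | >99.9% | 1.8 |

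Three or more are expected at 0.05 once m reaches about 3 / 0.0433 ≈ 70. At m = 20 the expected number is 0.87.

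**Step 3: any of the four samples may count.** In 20,000 simulated null data sets, the per-metabolite false-positive rate rose from 4.3% to 16.3%, 14.4%, 12.2% and 8.7% at within-patient correlations of 0, 0.5, 0.7 and 0.9. That is roughly 9 to 16 per 100 metabolites. Section 5.3 neither states nor excludes this practice.

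**Step 4: some metabolites truly differ.** This was simulated with 100 independent metabolites and a normal shift of 1.5 SD (assumed). With 10 true differences, about 30% of a list built on unadjusted p ≤ 0.05 is false on average; with 5, about 46%. Benjamini-Hochberg at 0.10 cuts the false share to about 8% in the 10-true case.

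**Step 5: what control costs.** Power per truly different metabolite, with 5 to 10 of 100 truly different:

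| Shift | Unadjusted 0.05 | Benjamini-Hochberg, q ≤ 0.10 |
|---|---|---|
| 1.5 SD | about 85% | 45–58% |
| 1 SD | about 51% | 9–12% |

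Bonferroni over 100 metabolites would leave about 22% at 1.5 SD, so a false discovery rule suits a search of this kind better.

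**The case against.** The strongest reply is that this is a declared exploration. Section 1 states the purpose as exploratory, section 5.2 repeats it, and section 3.2 speaks of clinical benefit only conditionally. Nothing in the protocol makes a treatment or diagnostic decision depend on the list. In a 10 v 10 discovery study, unadjusted reporting is defensible if it is labelled as such, and a separate analysis plan could add a threshold and an adjustment. The power loss in Step 5 is also a real cost. This stands in part and lowers the severity. It does not remove the point: section 5.2 uses the exploratory label to explain the absent sample size calculation, not to present the list as unadjusted, and the protocol's own statistical section names tests for the primary endpoint without a rule for reading them.

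Three stronger readings are tempting, and the documents do not support them:
- A reader might infer that the protocol declares every nominally significant metabolite to be cachexia-related. It says only that levels were compared; no threshold or declaration rule appears.
- A reader might infer that the secondary intra-day endpoint is protected across metabolites while the primary is left open. The Bonferroni correction most naturally covers comparisons among the four time points within one metabolite. On that reading, the protocol is silent on multiplicity across metabolites for both endpoints.
- A reader might infer that several false metabolites will certainly be found. That depends on a significance level and a metabolite count that the protocol does not give; at 0.01 with 100 metabolites, about one is expected.

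**Conclusion.** The point holds at moderate severity. As written, the primary endpoint rests on one rank test per metabolite, with no error control across metabolites and no criterion for calling a metabolite related. If no metabolite differs, about 2.2 / 4.3 / 8.7 false identifications are expected for 50 / 100 / 200 metabolites at an assumed two-sided 0.05, or about 0.4 / 0.9 / 1.8 at an assumed 0.01, and more if any time point may count. Both the significance level and the metabolite counts are assumptions. Correlation between metabolites leaves these expected counts unchanged but makes the actual count more variable. The false shares and power figures rest further on independent metabolites, a normal shift and an assumed number of true differences.

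**What to change.** In section 5.3:

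1. Name one between-cohort test per metabolite, on one prespecified time point or one per-patient summary of the four samples.
2. Apply Benjamini-Hochberg across all metabolites from both platforms together, and state how many were tested.
3. Report the raw p-value and the q-value for every metabolite.
4. Call a metabolite cachexia-related only if it meets a false discovery level fixed in advance, for example q ≤ 0.10. That level is a choice; what matters is that it is set before the data are seen.
5. State the nominal significance level, and label metabolites that pass it but miss the q-value cut-off as unadjusted and hypothesis-generating.

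The cost is a few sentences and trivial programming, with no extra patients or samples. The smallest attainable p at 10 v 10 is far below any cut-off needed here, so the rule can be met. The real price is fewer declared metabolites and the loss of power shown in Step 5, which is severe near 1 SD. Keeping all raw p-values in the report softens that loss, since weaker signals stay visible for later studies.
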